### Data management

Secure collection of data is performed. Data entry will be performed using a predefined case report form (CRF) (Additional file 2) with accompanied data entry protocol. This provides instructions units to be used, missing data handling and range checks.

### Statistical methods

All statistical tests will be two-sided and a *p* value < 0.05 is considered to be significant. Statistical analyses will be performed using IBM SPSS version 24 (IBM Corporation, Armonk, NY, USA). Data will be analyzed following intention-to-treat and per-protocol. Missing data will be handled using multiple imputation. Descriptive statistics will be used for all outcome measures.

A Fisher’s exact test or Chi-squared test will be performed to test the reduction in the rate of telangiectasia in the study groups at two-year follow-up, i.e. to test the hypothesis that the rates of telangiectasia in both study groups are equal (superiority study).

Local recurrence-free survival as well as overall and disease-specific survival rates at five and ten years will be estimated using the Kaplan–Meier method. The local recurrence rate will be reported at five and ten years. A Fisher’s exact test or Chi-squared test will be performed to test the difference in proportions (six-month, one-year and two-year cumulative rate of side effects, skin dose > 90% over at least 1 cm^2^ at post-planning) between groups. (Skin) dosimetry data will be compared using a Mann–Whitney U test or an unpaired Student’s t-test depending of distribution of data. To study the effect of spacer on cosmesis (BCTOS questionnaire) and quality of life (EORTC-QLQ-C30/BR23 and EQ5-D questionnaire) over time, a repeated measurements analysis will be performed (linear mixed model, covariance structure: unstructured) with independent variables time, allocated group, and interaction effects between time and allocated group.

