### Eligibility and exclusion criteria

Eligibility criteria were derived from international guidelines [31, 32] for suitable patients for partial breast radiotherapy. Eligible patients are females aged ≥ 50 years with a confirmed histological diagnosis of invasive ductal carcinoma (IDC) and/or papillary, tubular, cribriform or medullar carcinoma and/or ductal carcinoma in situ (DCIS), after breast-conserving surgery with axillary node dissection (with a minimum of six nodes sampled) or sentinel lymph node biopsy. The maximum dominant tumor size is 3 cm and the tumor must be excised with negative surgical margins at ink for invasive carcinoma and ≥ 2 mm negative margins for DCIS or have a negative re-excision. The PBSI should be deemed technically feasible based on the seroma location, visibility, and size performing an ultrasound; the total implanted volume should be < 150 cc. Patient should have signed an informed consent.

Ineligible patients include those with lymphovascular invasion, lobular features on histology (pure or mixed) or sarcoma histology, triple negative tumors, extensive in situ carcinoma, multicentric disease (in more than one quadrant or separated by ≥ 2 cm), bilateral breast cancer, recurrent breast cancer, Paget’s disease of the nipple, metastases or active other cancer (defined by any malignancy in < 5 years, excluding any cured non-melanoma skin cancer or cervical cancer), neoadjuvant chemotherapy, known allergy for hyaluronic acid, active auto immune disorder with severe vasculitis component, uncontrolled and complicated insulin-dependent diabetes, pregnancy, cosmetic breast implants, psychiatric or addictive disorder that would preclude attending follow-up, or postoperative wound infection or abscess following Centers for Disease Control and prevention (CDC) criteria.

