### Outcomes

The primary endpoint of this trial is the occurrence of telangiectasia at two years after PBSI. Assessment is performed by a blinded physician, following the Bentzen’s 4-point scale which is included in the LENT/SOMA questionnaire [34, 35]. This scale is defined as: “none;” grade I, “< 1 cm^2^,” grade II, “1–4 cm^2^;” and grade III, “> 4 cm^2^.” Patients will also be blinded for the allocated treatment. The secondary outcomes include the local recurrence rate at five and ten years, the disease-free and overall survival rates at five years, as well as brachytherapy and spacer injection adverse events (AE) according to the commonly used NCI Common Toxicity Criteria for Adverse Events (CTCAE v 4.03) scale for acute side effects [36], practically occurring within three months of the brachytherapy, and the Radiation Therapy Oncology Group (RTOG)/ European Organisation for Research and Treatment of Cancer (EORTC) scoring systems for late side effects [37], practically occurring after three months. The symptoms include the experience of pain, skin redness, pigmentation, induration, dermatitis, subcutaneous induration, and the occurrence of infection at the site of spacer injection. Additionally, patient-reported outcome measures (PROMs) include the cosmetic result with the Breast Cancer Treatment Outcome Scale (BCTOS) questionnaire [38], using a validated Dutch version which will shortly be published by our group [39] and the health-related Quality of Life using the Dutch version EORTC QLQ-C30 and BR23 questionnaires, version 3 [40]. Ipsilateral breast recurrence must be proven getting a copy of the biopsy or the salvage surgery pathology report. Dosimetry outcomes include the PTV volumes receiving at least 100% or 200% of the prescribed dose (V_100_ and V_200_) as quality assurance for all treatment plans and maximum dose to a small skin volume of 2 mm thickness over 1 cm^2^ (D_0.2cc_) [21, 41] and the presence of a hotspot (isodose ≥ 90%) [42] on 1 cm^2^ of the skin as indicators of skin toxicity risk.

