Outcomes are collected before the PBSI implantation at baseline, at the end of the procedure, and at two months, six months, and every year up to five years, during follow-up visits at the cancer center. If a patient does not attend a follow-up appointment, she will be called and/or her family doctor contacted. Reason for no-show will be recorded in order to ensure exhaustive capture of survival, recurrence, and/or AEs. Overall and disease-specific survival will be assessed until 10 years through GBA (Population registry, Gemeentelijke Basis Administratie) and/or general practitioners. A summary of the timing of questionnaires is detailed in Fig. 1.

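### Kaplan–Meier for ten-year disease-specific survival censors other-cause deaths, so its complement slightly overstates the probability of breast-cancer death; local recurrence shares this only if read from a recurrence-only curve

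*Protocol article*

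**What the plan says.** The Statistical methods section of the protocol article names one time-to-event estimator for three oncological outcomes: "Local recurrence-free survival as well as overall and disease-specific survival rates at five and ten years will be estimated using the Kaplan–Meier method". The next sentence deals with recurrence itself and names no estimator: "The local recurrence rate will be reported at five and ten years".

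The Outcomes section lists "the local recurrence rate at five and ten years, the disease-free and overall survival rates at five years" among the secondary outcomes. On follow-up it says "Overall and disease-specific survival will be assessed until 10 years through GBA" and/or general practitioners, and places the clinic assessments "at two months, six months, and every year up to five years, during follow-up visits at the cancer center".

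On age, the eligibility section says "Eligible patients are females aged ≥ 50 years", and neither the inclusion nor the exclusion list gives an upper limit.

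The article does not define local recurrence-free survival (whether death is an event or is censored). It mentions no competing-risk method, names no between-arm test for these outcomes, and gives no expected rate of recurrence, breast-cancer death or other-cause death.

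**The concern.** In disease-specific survival only a breast-cancer death is an event. A woman who dies of something else can no longer have the event, yet Kaplan–Meier censors her, which treats her as if she could still have it later. One minus the curve then estimates the probability of breast-cancer death in a hypothetical population where nobody dies of anything else. Whenever other-cause deaths occur, this is higher than the proportion who actually die of breast cancer. A ten-year horizon and no listed upper age limit make such deaths likely.

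Local recurrence depends on a definition the article does not give:

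- If the rate comes from a curve in which deaths are censored, it is overstated in the same way.
- If death is an event in local recurrence-free survival, Kaplan–Meier is correct for that composite, but its complement mixes recurrence with death and is not a recurrence rate.

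On neither reading does the complement of the one named recurrence curve give the actual probability of local recurrence.

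At stake are the absolute rates. The Discussion expects no effect of the spacer on oncological results but says that the supporting pre-clinical finding on target coverage still needs clinical confirmation. Readers will look to the recurrence and cancer-death figures for this.

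**Working it through.** **Figures in the plan.** There is none to reproduce for these outcomes. The only design figures concern telangiectasia. From them I use only the total of 230 with 1:1 allocation, that is 230/2 = 115 per arm.

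**Assumed inputs.** F is the ten-year event rate read as one minus Kaplan–Meier, taken as 5% with 3% as an alternative. m is ten-year mortality from the competing cause, taken as 10–30%. For disease-specific survival this is other-cause death; for a recurrence-only curve it is death without recurrence. Hazards are constant.

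**Formulas.** h1 = −ln(1 − F)/10; h2 = −ln(1 − m)/10; cumulative incidence at ten years = h1/(h1 + h2) × [1 − exp(−10(h1 + h2))].

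**Worked case, F = 5%, m = 20%.** h1 = 0.00513 and h2 = 0.02231, so h1/(h1 + h2) = 0.1869. The bracket is 1 − 0.95 × 0.80 = 0.24. Cumulative incidence = 0.1869 × 0.24 = 4.49%.

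**Ten years, F = 5%:**

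| Competing mortality m | 1 − KM | Cumulative incidence | Excess (points) | Ratio |
|---|---|---|---|---|
| 10% | 5.00% | 4.75% | 0.25 | 1.05 |
| 15% | 5.00% | 4.62% | 0.38 | 1.08 |
| 20% | 5.00% | 4.49% | 0.51 | 1.11 |
| 30% | 5.00% | 4.21% | 0.79 | 1.19 |

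For F = 3% the cumulative incidences are 2.85, 2.77, 2.69 and 2.53%, with almost the same ratios. At five years, with the same hazards as F = 5%, one minus Kaplan–Meier is 2.53% and the excess is 0.07, 0.14 and 0.21 points for m = 10, 20 and 30%.

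**Wider range.** For F of 2–10% and m of 5–40%, the ten-year excess runs from 0.05 to 2.13 points. For F = 5% it passes 1 point only at m of about 40% (1.08 points).

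**Against sampling error.** With 115 per arm and a 5% rate, the simple binomial standard error is √(0.05 × 0.95/115) = 2.03 points, before further censoring. The excess is 0.25/2.03 = 0.12 to 0.79/2.03 = 0.39 of one standard error.

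**Between arms.** Suppose the Kaplan–Meier rates are 5% and 3% and m = 20% in both arms. The cumulative incidences are 4.49% and 2.69%. The ratio is 1.67 on either scale (5/3 and 4.49/2.69), and the difference is 1.80 instead of 2.00 points.

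**If death is an event in local recurrence-free survival.** With F = 5% and m = 20%, the complement of the curve is 1 − 0.95 × 0.80 = 24%, against a recurrence probability of 4.49%. It describes a different quantity.

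**The case against.** The case on the other side has four parts.

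**Estimand.** Kaplan–Meier disease-specific survival is a conventional net estimate and is valid as such if other-cause death is independent of cancer death. The article does not say that the crude probability is the target. This stands as a matter of wording: the curve is not wrong for the net quantity. The error lies in reading its complement as the proportion of women who die of breast cancer.

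**Missing detail.** Event definitions and censoring rules for secondary outcomes are often left to the full protocol or analysis plan, and neither is shown. This stands for the undefined recurrence endpoint, which is no fault in itself. It does not remove the point on disease-specific survival, where the article states its estimator.

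**Local recurrence.** A reader might infer that the plan estimates the local recurrence rate by Kaplan–Meier and that this rate is therefore biased. The text does not support that. It assigns Kaplan–Meier to local recurrence-free survival and leaves the estimator of the recurrence rate open. Overall survival, in the same sentence, is correctly handled.

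**Consequence.** A reader might also infer that the judgement on the spacer's oncological safety is distorted, or that other-cause deaths will outnumber cancer events. Neither is supported. Randomised arms with similar other-cause mortality carry a similar excess, no between-arm test is named for these outcomes, and the documents give no mortality figures. The exclusions, among them "metastases or active other cancer (defined by any malignancy in < 5 years" and uncontrolled, complicated insulin-dependent diabetes, should lower other-cause mortality. This stands and keeps the priority low.

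**Conclusion.** The point holds at low priority. For disease-specific survival the direction is certain: once any other-cause death is censored, one minus Kaplan–Meier exceeds the actual probability of breast-cancer death. For local recurrence it is conditional on how the rate is obtained.

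Under constant hazards and an assumed 10–30% other-cause mortality at ten years, a 5% rate is overstated by 0.25–0.79 points (5–19% in relative terms), well under one standard error for an arm of 115. All event and mortality rates here are assumptions. The between-arm comparison is little affected provided other-cause mortality is similar in the arms. Telangiectasia at two years, the primary outcome, is not affected at all.

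**What to change.** Report breast-cancer death and local recurrence at five and ten years as cumulative incidence (Aalen–Johansen), by arm with 95% confidence intervals. The competing event is death from other causes for breast-cancer death, and death without recurrence for local recurrence. Keep Kaplan–Meier for overall survival and for local recurrence-free survival, and state that death counts as an event in the latter.

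The cost is a sentence or two in the analysis plan and a standard routine that may lie outside the named software. The reported figures change slightly. The analysis of breast-cancer death needs no new data, because disease-specific survival already requires cause of death.

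One limit: changing the estimator does not supply recurrence data. The article's clinic visits end at five years, and it extends only overall and disease-specific survival to ten, so the source of recurrence data after year five should be confirmed against the full protocol. The same revision should reconcile the disease-free survival listed under Outcomes with the disease-specific survival analysed under Statistical methods.

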### Interventions

The permanent seed implant procedure includes a computed tomography (CT) simulation done positioning the patient similarly to for external beam breast radiotherapy. The clinical target volume (CTV) corresponds to the seroma with a 1-cm margin, limited to the fascia pectoralis, and 5 mm below the skin; the planned target volume (PTV) is an additional expansion of 0.5 cm with the same skin and chest wall limits. A pre-implant plan is generated using the MIM Symphony® software (MIM Software Inc., Cleveland, OH, USA) to order stranded ^103^Pd seeds of 2.5 U activity.

For the procedure, anesthesia includes a non-steroidal anti-inflammatory drug (NSAID) for two days, light sedation with Propofol, and local freezing. Patients are positioned on a breast board, with the arm abducted similarly to the CT simulation. The breast skin is disinfected and the patient draped. The PTV projection perpendicular to the fiducial needle axis is outlined on the skin surface and verified using ultrasound. A PBSI template (Concure Oncology, Seattle, WA, USA) is attached to the fiducial needle and immobilized using a modified medical articulated arm (Fisso, Medtec Baitella Alt, Switzerland). The preloaded needles containing ^103^Pd strands are then inserted under US guidance [33]. In patients allocated to receive spacer, an amount of 4–10 cc of biodegradable hyaluronic acid (Barrigel™, Palette Life Sciences, Santa Barbara, CA, USA or Restylane SubQ®, Galderma Benelux, Breda, the Netherlands) is injected directly under the skin under ultrasound guidance covering the PTV projection, aiming to create an extra 0.5–1 cm space between the treatment volume and the skin. If the skin is judged not to be at risk in all projection quadrants, it could be decided to only inject the area at risk. The injected skin quadrants will be reported specifically. All radiation oncologists involved in this study are trained to perform the intervention and the injection procedure and reporting instructions are incorporated in trial protocols. The hyaluronic acid spacer is expected to be fully degraded after 3–9 months.

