Other secondary outcomes are brachytherapy and spacer injection AEs according to commonly used NCI CTCAE and RTOG/EORTC scoring systems for late side effects. Where our main hypothesis is that the spacer increases distance and reduces skin dose and telangiectasia, this will allow for analyzing the effect on other less radiotherapy-specific symptoms such as pain, skin redness, pigmentation, induration, dermatitis, subcutaneous induration, and the occurrence of infection at the site of spacer injection. Although hyaluronic acid is widely used as a dermal filler, the application as a skin spacer in patients treated with breast radiotherapy is a new concept and any unexpected side effects will be captured. Skin dose outcomes will potentially lead to updated skin dose constraints in treatment planning. Also, it could distinguish radiotherapy induced toxicity from other causes (i.e. intervention-related toxicity). PROMs assess the effect of the skin spacer on cosmesis, function, and quality of life. Furthermore, by using internationally recognized PROMs, a better comparison with other radiotherapy techniques is possible.

This clinical trial was designed because it is unknown whether the dosimetric benefit of the spacer, which was found in our pre-clinical study [44], translates in a real patient benefit. An example of a clinical trial that could not demonstrate that a dosimetric benefit translates into better patient outcomes, is the breast intensity modulated radiation therapy (IMRT) trial. In this trial, the improved radiation dose distribution and reduced moist desquamation using IMRT, compared to standard wedge RT, did not result in reduced long-term side effects such as chronic breast pain [43].

Our primary analysis will be done following the intention-to-treat principle: the effect of skin spacer on telangiectasia rate at two years. However, a per-protocol analysis will allow for a better definition of a successful skin spacer as the skin spacer injection protocol (> 5 mm in a PTV skin projection area) is not definite and the trial could be hypothesis-generating.

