A drawback of our study is that we are not able to secure a full double-blind design. Patients might be aware of an injected spacer as it could be palpable under the skin. For physicians, it might be possible to remember the allocated treatment after being unblinded during the PBSI procedure. However, with the assessment of the primary outcome at two-year follow-up, this memory effect is not likely to cause any bias. Also, the type of outcome measure (telangiectasia using Bentzen’s 4-point scale) allows for an objective, reproducible assessment. Furthermore, this a single-center study and our findings should be confirmed in a multicenter setting. Lastly, with only patients undergoing PBSI in this study, generalization of our findings to other APBI techniques should be done with caution. However, theoretically, this principle would hold for any APBI technique with a rapid dose fall off.

In this trial, we investigate the effect of a subcutaneous spacer injection on the skin dose, late skin toxicity, and cosmetic outcome in patients treated with PBSI in the setting of breast-conserving therapy. Our results will be relevant for most forms of breast brachytherapy as well as robotic radiosurgery, as skin spacers could be used to protect the skin with these other techniques.

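### For induration-type side effects, the two-year cumulative comparison can keep counting spacer gel that has already gone, so it does not measure long-term toxicity

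*Protocol article*

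**What the plan says.** Statistical methods plans a Fisher's exact or Chi-squared test between groups on the "six-month, one-year and two-year cumulative rate of side effects". It states no other between-group test for clinician-scored side effects.

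Outcomes uses two scales with two windows: CTCAE for acute effects, "practically occurring within three months of the brachytherapy", and the RTOG/EORTC "scoring systems for late side effects [37], practically occurring after three months". On content it says: "The symptoms include the experience of pain, skin redness, pigmentation, induration, dermatitis, subcutaneous induration, and the occurrence of infection at the site of spacer injection". After baseline and the end of the procedure, data are collected "at two months, six months, and every year up to five years".

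On the gel, given to the spacer arm only, Interventions says: "The hyaluronic acid spacer is expected to be fully degraded after 3–9 months". The Discussion adds: "Patients might be aware of an injected spacer as it could be palpable under the skin".

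**The concern.** A cumulative rate never drops an event that has resolved. That matters here because one arm receives 4–10 cc of material under the skin that an examiner may feel for some months and that is then expected to disappear, while induration and subcutaneous induration are among the scored items. A control patient cannot have a gel-related event, so any firmness of this kind that is scored adds to the spacer arm alone and is carried into its one- and two-year figures.

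The Discussion presents the trial as aiming to prevent long-term skin toxicity. A reader would naturally take a two-year side-effect rate as evidence on that. For induration-type items it could show an excess in the spacer arm when late tissue change is equal, or hide a real late benefit.

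**Working it through.** **1. Timing.**

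| Visit | Scale window | Gel present? |
|---|---|---|
| 2 months | acute (within 3 months) | yes, expected |
| 6 months | late (after 3 months) | possible (3–9 months) |
| 1 year | late | expected to be gone |
| 2 years | late | expected to be gone |

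If all events are counted, gel firmness at either early visit enters the later cumulative rates. If only late-scale events are counted, the two-month visit drops out but the six-month visit does not, because the expected life of the gel crosses the three-month line.

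**2. The plan's own figure.** The article states no side-effect rate and no power for side effects. The only figure borrowed is the 105 per arm in Sample size. It reproduces: for 22.4% v 7.7%, two-sided 0.05 and 80% power, the continuity-corrected formula gives 105, and the exact Fisher power at 105 per arm is 81.7%.

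**3. No true late difference.** Assumptions, none from the article: true late induration is 15% in both arms; gel is scored as induration in a proportion x of spacer patients; the two are independent. Then

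spacer cumulative rate = 1 − (1 − 0.15)(1 − x).

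The rejection probability is found by enumerating Fisher's exact test (two-sided, p < 0.05) at 105 per arm against a control rate of 15%.

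| x | Spacer rate | Trials rejecting |
|---|---|---|
| 0 | 15.0% | 3.1% |
| 2% | 1 − 0.85 × 0.98 = 16.7% | 4.1% |
| 5% | 1 − 0.85 × 0.95 = 19.3% | 9.4% |
| 10% | 1 − 0.85 × 0.90 = 23.5% | 28.6% |
| 20% | 1 − 0.85 × 0.80 = 32.0% | 79.8% |

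**4. A true late benefit.** Borrow 22.4% v 7.7% from the telangiectasia assumption purely as an example of a late effect. With the same test and formula, spacer rate = 1 − (1 − 0.077)(1 − x).

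| x | Spacer rate | Control minus spacer | Trials rejecting |
|---|---|---|---|
| 0 | 7.7% | 14.7 points | 82% |
| 5% | 12.3% | 10.1 points | 42% |
| 10% | 16.9% | 5.5 points | 13% |
| 20% | 26.2% | −3.8 points | direction reversed |

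**The case against.** The strongest defence is that the outcome is defined as brachytherapy and spacer-injection adverse events. Firmness caused by the gel is an adverse event of the intervention, and whether a patient ever had it is a legitimate safety question. On that view the rejections in step 3 detect a real difference. This stands, and it is why the cumulative rate should be kept. It does not make the two-year figure a measure of long-term toxicity.

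The rates are also assumed. The article says only that the gel could be palpable, which is not the same as being graded as induration. At x = 2% the effect is negligible.

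Four stronger readings are tempting, and the article does not support them:

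- A reader might infer that acute and late events are pooled and that grades from the two scales are mixed. Statistical methods does not say so. It mentions proportions, not grades, and does not say which scale feeds the rate. The fair statement is that it does not separate them.
- A reader might infer that late radiation toxicity cannot be isolated at all. Status is collected at one and two years, descriptive statistics are planned for all outcomes, and telangiectasia at two years has its own test and is described as a specific radiation marker.
- A reader might infer that the analysis defeats a stated aim, from the Discussion's remark that "it could distinguish radiotherapy induced toxicity from other causes". That remark follows a sentence on skin dose, may refer to dosimetry, and is a possibility rather than an aim set for these rates.
- A reader might conclude that the cumulative rate should be dropped. Its value as a safety summary argues against that.

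**Conclusion.** The point holds for the induration-type secondary items. As written, the only stated between-group comparison can carry resolved gel firmness into the one- and two-year rates of one arm, and this remains so if only late-scale events are counted. For these items the two-year cumulative comparison does not measure long-term toxicity, and any distortion runs against the spacer. The primary conclusion is not touched.

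The size cannot be fixed from the article. Under the assumed 15% late rate and independence, the chance of a significant difference with equal late toxicity goes from 3% to about 4%, 9%, 29% and 80% as gel scored as induration goes from none to 2%, 5%, 10% and 20%. The problem is trivial if such scoring is rare and serious if it reaches one patient in ten or more.

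**What to change.** Three changes to the analysis wording, settled before any between-group results are seen:

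1. Keep the cumulative rate as the safety summary, and state it separately for acute events (CTCAE, up to three months) and late events (RTOG/EORTC, after three months).
2. Add a between-group comparison of presence and grade at the one-year and two-year visits, and name it as the late-toxicity comparison.
3. Flag six-month results as obtained while the spacer may still be present.

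No new visits, scales or patients are needed. The cost is a few more secondary comparisons. Presence at a visit also misses late events that appear and resolve between visits, which the retained cumulative rate still covers.

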## Methods/design

### Aim and design

We propose a parallel-group RCT comparing the occurrence of telangiectasia at two years in PBSI patients with or without a subcutaneous spacer injection. Allocation ratio is 1:1 and the trial is designed to test the superiority of the intervention. The primary hypothesis for the trial assumes that an injected hyaluronic acid spacer will reduce skin dose of PBSI and eventually the rate of telangiectasia at two years, compared to patients undergoing PBSI without spacer. As the intervention is applied when the patient is sedated, a placebo injection as comparator was deemed unnecessary. The methods section is described according to the Standard Protocol Items: Recommendations for Interventional Trials (SPIRIT) 2013 checklist (see Additional file 1).

Eligible patients will be recruited at hospitals referring patients after breast-conserving surgery for adjuvant radiotherapy at the Erasmus MC Cancer Institute, a large University hospital in Rotterdam, where the PBSI technique can be performed in the Netherlands.

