### Sample size

Previous studies found 22.4% telangiectasia at two years [9]. We expect the use of a spacer could reduce the skin dose to 50% [21] and the occurrence of any telangiectasia (≥ grade 1) to 7.7% [43]. To test this reduction (e.g. the superiority of the intervention), 105 (Fisher’s exact test) patients per treatment arm would be needed (α = 0.05, β = 0.20). A sample size of 230 patients will allow for a 10% lost to follow-up rate.

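### The mixed model for cosmesis and quality of life makes no efficient use of the baseline score: its estimates are valid but less precise than a baseline-adjusted analysis and depend on chance baseline imbalance

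*Protocol article*

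**What the plan says.** For cosmesis and quality of life, the Statistical methods section of the Protocol article states that "a repeated measurements analysis will be performed (linear mixed model, covariance structure: unstructured". The instruments analysed this way are BCTOS, EORTC QLQ-C30/BR23 and EQ5-D. The section then fixes the model terms: "with independent variables time, allocated group, and interaction effects between time and allocated group". No other model term is listed.

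On timing, the Outcomes section states: "Outcomes are collected before the PBSI implantation at baseline, at the end of the procedure, and at two months, six months, and every year". The yearly visits run to year five. For the questionnaire schedule the section refers to Fig. 1, and that figure is not reproduced in the text at hand.

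These scales are secondary outcomes: "patient-reported outcome measures (PROMs) include the cosmetic result with the Breast Cancer Treatment Outcome Scale (BCTOS) questionnaire". The primary endpoint is telangiectasia at two years. The article does not say whether the baseline score is one of the time levels of the response. Nor does it say whether the spacer effect is the arm difference at a visit or the time-by-group contrast against baseline.

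**The concern.** A pre-treatment score usually predicts later scores on the same questionnaire. In a randomised trial it can be used to reduce the variance of the treatment effect and to remove the influence of whatever baseline difference chance has produced. The listed terms do neither efficiently:

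- If baseline is outside the response, each visit effect is a plain difference between arm means.
- If baseline is a time level with a free group effect, the model lets the arms differ at a visit that precedes the intervention. The effect is then again a plain visit difference, or a difference in change from baseline.

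The stake is the precision of the patient-reported results. The Discussion says the trial exists because it is unknown whether the dosimetric gain reaches the patient, and it assigns cosmesis, function and quality of life to these questionnaires. The sample size was set on telangiectasia alone, so the documents plan no power for these outcomes.

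**Working it through.** **The plan's own figure.** The article states no figure for this model. Its only sample size is 105 per arm for telangiectasia, 22.4% against 7.7% (two-sided 0.05, 80% power). The continuity-corrected two-proportion formula gives 105, and exact Fisher power at 105 per arm is 81.7%. That figure is reproduced; 105 serves below only as the number per arm.

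**Inputs.** From the article: 1:1 allocation, two-sided 0.05, n = 105 per arm. Assumed: a correlation ρ between baseline and the follow-up score, and equal standard deviations at both times and in both arms. The documents do not give ρ, so a range is shown.

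**Variance at one follow-up visit, complete data, in units of 2·SD²/n**

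- Visit difference: 1
- Change-from-baseline contrast: 2(1 − ρ)
- Baseline-adjusted (covariate or equal-baseline constraint): 1 − ρ²

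The ratios to the adjusted analysis are 1/(1 − ρ²) and 2(1 − ρ)/(1 − ρ²) = 2/(1 + ρ).

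| ρ (assumed) | Adjusted variance | Visit difference ÷ adjusted | Change contrast ÷ adjusted |
|---|---|---|---|
| 0.3 | 0.91 | 1/0.91 = 1.10 | 1.40/0.91 = 1.54 |
| 0.5 | 0.75 | 1/0.75 = 1.33 | 1.00/0.75 = 1.33 |
| 0.7 | 0.51 | 1/0.51 = 1.96 | 0.60/0.51 = 1.18 |
| 0.8 | 0.36 | 1/0.36 = 2.78 | 0.40/0.36 = 1.11 |

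Both ratios exceed 1 for every ρ between 0 and 1. If the baseline SD is k times the follow-up SD, the change contrast has variance 1 + k² − 2ρk = (k − ρ)² + (1 − ρ²). Its ratio then shifts but cannot fall below 1.

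**Check on the repeated-measures model.** A generalised least squares fit of the full time-by-group model (four visits including baseline, ρ = 0.5, complete data) returned exactly the raw arm differences at each visit. Relative variances were 1.00 for the visit difference, 1.00 for the change contrast and 0.75 with baseline means constrained equal. So the unstructured covariance does not recover the precision by itself.

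**What this means at ρ = 0.5.** For an illustrative effect of 0.389 SD at 105 per arm:

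- Unadjusted: SE = √(2/105) = 0.138; 0.389/0.138 − 1.96 = 0.86; power about 80%.
- Adjusted: SE = 0.138 × √0.75 = 0.120; 0.389/0.120 − 1.96 ≈ 1.29; power about 90%.

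Equivalently, 80% power needs 104 per arm without adjustment and 78 with it (104 × 0.75 = 78).

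**Chance imbalance.** The baseline difference between arms has standard error √(2/105) = 0.138 SD, so a 95% range of about ±0.27 SD. The visit difference carries ρ times that imbalance and the change contrast carries −(1 − ρ) times it. In 20,000 simulated trials at ρ = 0.5 the slopes on the imbalance were +0.50, −0.50 and, for the adjusted estimate, −0.003. An imbalance at the edge of the range therefore moves the first two by about 0.5 × 0.27 = 0.135 SD, in opposite directions. All three estimators averaged about zero under no effect.

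**The case against.** The strongest reply is that this is a standard and valid model in a condensed article. Several parts of that reply stand.

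- A reader might infer that the baseline score is ignored altogether. The documents do not establish this. An analysis over time, with baseline as the first collection point, may well carry baseline as a time level. The interaction contrast then compares changes from baseline, so baseline is used, only inefficiently, and imbalance is over-corrected rather than left in.
- A reader might infer that the results would be biased. They would not: under concealed 1:1 allocation both contrasts are unbiased on average. The issue is efficiency and dependence on chance imbalance.
- A reader might infer that the trial's main conclusion is weakened. It is not: hypothesis, primary test and sample size all concern telangiectasia.
- The statement that outcomes are collected at baseline is general. The questionnaire schedule is in a figure not shown, so a baseline for each instrument is likely but not confirmed.
- The size depends wholly on an assumed correlation. Under the change contrast the loss shrinks to 1.18 at 0.7 and 1.11 at 0.8.
- How baseline enters the response and which contrast is reported are details that an analysis plan may settle. Their absence is not the point here.

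What does not stand is leaving the whole matter to an unseen plan. The article fixes the model type, the covariance and the independent variables, and under either reading of those terms the estimate is less precise than one that uses the baseline score fully.

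**Conclusion.** The point holds as a matter of efficiency for secondary outcomes. With only time, group and their interaction, the spacer effect on cosmesis and quality of life is a visit difference or a change-from-baseline contrast. Relative to baseline adjustment, the variance is higher by 10% to 96% for the visit difference and by 18% to 54% for the change contrast, over assumed correlations of 0.3 to 0.7 with equal standard deviations at baseline and follow-up. At 0.5 the loss is worth a quarter of the sample under either contrast.

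These figures are for a single visit with complete data, and they presuppose that each questionnaire is given before implantation. The change is worth making, but nothing in the stated model is invalid.

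**What to change.** Amend the model statement in one of two ways, keeping the unstructured covariance:

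1. Keep baseline as a response level and constrain the arm means to be equal there, that is, fit arm effects at post-baseline visits only. This retains patients who lack a baseline score.
2. Model post-baseline visits only, with visit, arm, arm-by-visit, baseline score and baseline-by-visit.

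In the same sentence, name the contrast to be reported, for example the two-year arm difference with its 95% confidence interval.

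No new data are needed if the questionnaires are given at baseline. The second version adds a few parameters, and patients without a baseline score would need imputation; the article already plans multiple imputation for missing data. Because recruitment began in September 2017, the change should be dated and made before outcome data are examined by arm.
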